### Randomization

Randomization will be performed by a staff member of the Department of Psychosomatics and Psychotherapy after finishing the diagnostic assessment at T0. People get randomized in a 1:1:1 ratio to a) inhibitory control training with feedback and post-assessment, b) inhibitory control training without feedback and post-assessment, c) waitlist-control and post-assessment. All arms undergo the four- and twelve-week follow-up.

### Blinding

The raters assessing psychopathology are blind regarding the treatment condition. Patients who are randomised to the a) inhibitory control training with feedback and b) the inhibitory control training without feedback will be blinded towards treatment conditions, i.e. prior to the study they will be informed that only one element of the training differs between the two conditions, and they will be informed about this difference in more detail after termination of the study. Raters conduct the appointment T0, T8 and T9 which are separate from the intervention (T1-T6)/waitlist-control and post-assessment (T7) appointments, thus ensuring blinding to the treatment condition.

### Data management

All data is assessed pseudonymized. Data will predominantly be entered manually by either the study personnel or patients themselves for self-report measures. Data from paper-based source data will later be transferred to an electronic study database and fidelity and plausibility to the source data will be checked at random by the study staff. All trial data will be stored in line with the European General Data Protection Regulation 2018.

### Statistical methods

The primary analysis will use the number of binge eating episodes during the last four weeks in a linear mixed model with baseline adjustment at T8 and T9. In case of non-normally distributed data we want to use generalized linear mixed models as this statistical approach accounts for non-normally distributed data better. To test for noninferiority of the inhibitory control training without feedback compared to the inhibitory control training with feedback, we perform one tailed-tests with an alpha-level of 0.025. Further, we compare if the confidence interval of the inhibitory control training without feedback includes the effect of the inhibitory control training with feedback which resembles the non-inferiority margin [3, 37, 53]. For comparison of inhibitory control training with feedback against the waitlist control and for the comparison of inhibitory control training without feedback against the waitlist control we conduct two-sided tests with an alpha-level of 0.05.

In secondary analyses, a mixed model approach will be used to analyze the secondary outcomes also with baseline adjustment. Effect sizes will be analyzed and reported for primary and secondary outcomes. For binary outcomes, odds ratios and for quantitative outcomes, standardized differences will be reported. Primary parameters will be time vs. treatment interactions at several time points after baseline.

Further, for the regression analyses, a mixed model approach will be used as well. We want to investigate the impact of sociodemographic, comorbid psychopathology (SKID-V, BDI-II), self-efficacy (URICA-S, IE-4, food-related self-efficacy), self-esteem (RSE), treatment expectation (self-developed self-report questionnaire) as predictors on the primary outcome.

Last, for potential mechanisms underlying the inhibitory control training, we will conduct mixed models on the valence ratings of the different food stimuli and its relation to the primary outcome.

There will be no interim analysis. The primary analysis will be done for the intent to treat population, which is defined by including all patients who attended the baseline assessment. Multiple imputation will be used for subjects dropping out according to the method of Rubin. The imputation model will use 500 replications and will include age, gender and baseline assessment. Furthermore, available values from preceding visits will be included. Analyses will be performed using SPSS for Windows (Version 28.0.0.0) and R (Version 4.2.2.) using the packages *lme4* [6], *lmerTest* [34] and *emmeans* (Lenth, 2019).

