#### Primary outcome measure

Binge eating frequency in the last four weeks according to the Eating Disorder Examination (EDE) [26] will serve as a primary clinical outcome. EDE is a standardized structured expert interview to assess eating disorder psychopathology. It has shown high inter-rater reliability (Cohens Kappa > 0.80) and internal consistency(Cronbach’s Alpha 0.73 for the subscales; 0.93 for the total score) indicating a good quality of the interview on a superordinate level [26]. EDE includes diagnostic items as well as items related to the four subscales restraint, eating concern, weight concern and shape concern. The diagnostic item 10 is assessing the binge eating frequency in the past four weeks. We compare changes in binge eating episodes at the four weeks follow-up (T8) to baseline (T0) and at the 3-months follow up (T9) to baseline (T0). Binge eating frequency is of high clinical relevance as binge eating resembles the core pathology of eating disorders with regular binge eating [4].

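### Binge eating frequency is primary at both T8 and T9 with no deciding visit or success rule, each contrast is tested at full alpha, and the named interaction parameter is ambiguous

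*Protocol article*

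**What the plan says.** - **Visits.** Under Primary outcome measure, changes in binge eating episodes are compared "at the four weeks follow-up (T8) to baseline (T0) and at the 3-months follow up (T9) to baseline (T0". Under Statistical methods, the primary analysis places the outcome "in a linear mixed model with baseline adjustment at T8 and T9". Table 1 marks the primary outcome at both visits. The two are not ranked.
- **Contrasts.** For training without against training with feedback (non-inferiority), "we perform one tailed-tests with an alpha-level of 0.025". For each training against waitlist, "we conduct two-sided tests with an alpha-level of 0.05". The Current study section applies the non-inferiority hypothesis and both superiority hypotheses to the primary outcome.
- **Parameter.** The next paragraph of Statistical methods, which opens with secondary analyses, states: "Primary parameters will be time vs. treatment interactions at several time points after baseline".
- **Aim.** The Current study and Discussion sections make the role of feedback the overarching question and primary aim. They do not name a deciding visit or test.

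**The concern.** A primary analysis should lead to one identifiable result. Here three contrasts at two visits give six tests of the primary outcome. Each has its full nominal level, and no rule says what counts as success. If T8 and T9 disagree, the text supports a claim from either, and the nominal error rates then no longer describe the procedure.

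The parameter is also described in two ways. One sentence implies an arm contrast at T8 and T9 given baseline. Another names time-by-treatment interactions as primary. Depending on how T0 enters the model, these may be the same quantity or different ones.

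Non-inferiority to the training with feedback also means little unless that training is shown to work, and the tests are not linked on this point.

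**Working it through.** **Inputs from the protocol article.** Sample size section: 20 per group, d about 0.7, 5% dropout, 21 per arm, 63 in total. Statistical methods: the alpha levels above. **Assumed:** a T8-T9 correlation r of 0.4, 0.6 or 0.8, because the article gives none.

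**The plan's own figure.** 20 × 1.05 = 21 per arm, and 3 × 21 = 63, as stated. (Dividing instead gives 20/0.95 = 21.05.) At 21 per arm, 21 × 0.95 = 19.95, so about 20 are evaluable. The article states no power or overall error rate. With 20 per arm, d = 0.7 and two-sided 0.05, a single contrast at a single visit has power Φ(0.7 × √(20/2) − 1.96) = Φ(0.254) = 0.60 (0.58 by t test), before any gain from baseline adjustment.

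**Error rates if either visit may win.** Let Z8 and Z9 be the test statistics of one contrast, standard normal with correlation r under the null.

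- One waitlist contrast: 1 − P(|Z8| < 1.96 and |Z9| < 1.96).
- Non-inferiority, at the margin at both visits: 1 − P(Z8 < 1.96 and Z9 < 1.96).
- Four waitlist tests, all arms equal: as the first line, over four statistics. The two contrasts correlate 0.5 within a visit because they share the waitlist arm, and 0.5r across visits.

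| | nominal | r = 0.4 | r = 0.6 | r = 0.8 |
|---|---|---|---|---|
| One waitlist contrast, two visits | 0.05 | 0.093 | 0.088 | 0.078 |
| Four waitlist tests | 0.05 each | 0.166 | 0.156 | 0.139 |
| Non-inferiority, two visits | 0.025 | 0.047 | 0.044 | 0.039 |

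Simulation with 20 per arm gave 0.097, 0.086 and 0.078 for the first row and 0.168, 0.154 and 0.139 for the second. With one visit only, the two waitlist contrasts together still give about 0.09, so part of the 14-17% comes from having two contrasts, not two visits.

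**If both visits must succeed.** For one waitlist contrast with no effect at either visit, the error rate is 2 × 0.05 minus the first row: 0.007 to 0.022. It cannot exceed 0.05. Power at d = 0.7 at both visits is P(Z8 > 1.96 and Z9 > 1.96) with both means equal to 0.7 × √10 = 2.21. This is 0.42, 0.46 and 0.50 for the three correlations, against 0.60 at one visit.

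**The interaction.** Let δ8 and δ9 be the arm differences at T8 and T9.

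- *Baseline as covariate, T8 and T9 as outcomes.* Each pair of arms has one interaction, δ9 − δ8. For a sustained benefit it is zero. In simulation (d = 0.7 at both visits, 20 per arm, r = 0.6) it was significant in 5% of trials, against 57% for the T8 contrast.
- *T0 as an outcome level and reference.* The interaction at T8 is the arm difference in change from T0 to T8. Randomisation makes the arms equal at T0 in expectation, so this equals δ8. The standardised change difference is 0.7/√(2(1 − ρ)), with ρ the assumed T0-T8 correlation. For ρ = 0.4, 0.6 and 0.8, t-test power at 20 per arm is 0.50, 0.67 and 0.93.

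**The case against.** **Separate hypotheses in a proof-of-principle trial.** Distinct hypotheses may each be tested at their own alpha, and the feedback question is the stated primary aim. Multiplicity procedures and test order are often left to an analysis plan, which is not shown here. This stands as far as the lack of adjustment across the three contrasts goes. It does not resolve the visits: even with feedback non-inferiority as the only primary contrast, two unranked visits remain.

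**No rule says that either visit suffices.** True. If both were required, alpha would not inflate. The article states neither rule, so the inflation figures are conditional.

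**A reader might infer that a lasting effect would be invisible to the primary analysis.** The text does not support this. The interaction sentence stands in the paragraph on secondary analyses. Its reference to several time points after baseline fits T0 as the reference level better than a model with only T8 and T9 as outcomes, which has one interaction per pair of arms. The comparison of 5% with 57% belongs to that second model only. What stands is a conflict: the sentence calls these parameters primary, while the same section specifies baseline adjustment.

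**A reader might also quote an error rate of 23-25% over six tests.** The sum 4 × 0.05 + 2 × 0.025 = 0.25, or 0.226 under independence, is only an upper bound. With a positive margin, the non-inferiority null and both superiority nulls cannot all be true together.

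**Non-inferiority to an ineffective training.** The waitlist arm and the superiority tests address this by design. Only the link between the claims is unstated.

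**Conclusion.** The concern holds for the visits. The protocol article makes the primary outcome primary at T8 and T9 without a deciding visit or success rule, and sets full alpha for every contrast. If either visit may win, the false-positive rate is about 8-10% instead of 5% for one training-versus-waitlist contrast, about 14-17% over the four waitlist tests, and about 4-5% instead of 2.5% for non-inferiority. These figures assume a T8-T9 correlation of 0.4 to 0.8 and approximately normal test statistics.

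The interaction sentence is ambiguous, not shown to be wrong: it matches the intended contrast under one model and misses it under another. Loss of a sustained effect is not established. Nor do the documents show that one particular testing order is required.

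**What to change.** Before analysis, amend the Primary outcome measure and Statistical methods sections.

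1. Name one deciding visit, for example T8 with T9 secondary, or require success at both. Nothing in the article ranks T8 above T9, so the choice is the sponsor's.
2. Define the primary parameter as the baseline-adjusted arm contrast at that visit (at each visit, if both must succeed).
3. Delete the interaction sentence, or restrict it to the question whether the effect changes from T8 to T9.
4. State which contrast is primary. If it is feedback non-inferiority, interpret the result as non-inferiority to an effective training only if the training with feedback beats waitlist.

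**Cost.** Wording only. With one deciding visit, an effect seen only at the other becomes supportive. Requiring both lowers power for one waitlist contrast at d = 0.7 from 0.60 to 0.42-0.50. Keeping both visits with alpha split in two lowers it to 0.49, and 80% power would need 39 instead of 33 evaluable per arm.

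A three-step fixed order (with feedback versus waitlist, without feedback versus waitlist, then non-inferiority) is an option, not a required change. It puts the primary aim behind two gates. At d = 0.7 and 20 per arm each gate passes in about 58% of trials and both in about 41%, so about 59% of trials of effective trainings could make no formal claim about feedback.

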### Current study

As the food-modified antisaccade training alone produced strong effects in our previous trial [19], including decreases of binge eating frequency, eating disorder pathology, and antisaccade performance independently from the tDCS condition, we now investigate mechanisms underlying the effects of the food-modified antisaccade training without neuromodulatory support through tDCS. This proof-of-principle trial will investigate the role of feedback in the food-modified antisaccade training to reduce binge eating. In a randomized controlled parallel group design two conditions of the inhibitory control training are implemented: a) with feedback and b) without feedback. Both will be compared to c) no treatment. The superordinate research question of the project is to investigate the role of feedback in the food-modified antisaccade training to reduce regular binge eating behaviours. In more detail, we propose:Noninferiority of the food-related antisaccade training without feedback compared with the original training including feedback in patients with regular binge eating regarding binge eating frequency (primary outcome) and eating disorder pathology, impulsivity, task performance, motivation and self-efficacy (secondary outcomes).Confirmation of clinically relevant effects of the training without feedback against the waitlist control and confirmation of clinically relevant effects of the training with feedback against the waitlist control i.e. superiority in comparison with a group with no treatment regarding primary and secondary outcomes.We will perform regression analyses concerning impact of sociodemographic variables and psychopathology and the treatment outcome depending on the training condition.Subordinate, we are interested in mechanism-driven pathways of effective treatment with ICT in patients with regular binge eating behaviour. Thus, we exploratory investigate the pathways between the primary outcome and secondary outcomes, that also serve as predictors and moderators.

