### Sample size

We base our intended sample size on our randomized-controlled clinical pilot trial [19], where 20 patients per group were sufficient to detect significant effects with a moderate effect size between two groups (treatment vs. active comparator; d ≈ 0.7). With an expected dropout rate of 5% according to Giel et al. [19], we decided to allocate 63 patients in our current trial (n = 21 per study arm).

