## Discussion

The MINDBinges trial aims to identify the underlying mechanisms of a food-related inhibitory control training for individuals suffering from regular binge eating, as seen in BED, BN, OSFED and UFED with regular binge eating behaviour. This trial seeks to enhance our understanding of factors predictive of effective treatment, thereby enabling the development of more targeted cognitive trainings that address specific facets of eating disorder pathology.

The primary aim of this trial is to disentangle the role of feedback and its clinical relevance within cognitive trainings. To the best of our knowledge, this is one of the first studies in the domain of eating disorders investigating the role of feedback on task performance on clinical outcomes. This study builds on findings from a previous clinical RCT, which demonstrated a significant strong reduction in binge eating in a clinical population following six sessions of the same food-related inhibitory control training [19]. As in the prior study, we employ an individualized training approach by selecting food stimuli according to personal preference. The primary outcome reflects high clinical relevance as binge eating frequency is the core pathology of the assessed eating disorders (American Psychiatric Association and Association, 2013). Importantly, a lived experience representative has been part of the study team from the beginning of the project and was involved in the conceptualization of the whole study, especially regarding the development of the research questions. The perspective of this lived experience representative on the role of feedback is summarized in Box 1. The role of feedback is hypothesized to have a valuable role in optimizing inhibitory control trainings. To assess longer-term changes, we also stick to a comparably long follow-up period, enabling conclusions on partial or full remission of study patients. Additionally, we also investigate the superiority of the treatment against a waitlist control which was absent in the previous trial. Finally, by adopting a transdiagnostic approach and using a broad range of questionnaires for an in-depth characterization of the study population which might offer chances in subgroup-typical specifics in adapting and increase specifity of cognitive trainings.

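### The stated non-inferiority criterion defines no allowable loss: it compares the no-feedback arm's confidence interval with the feedback arm's own effect and calls that effect the margin

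*Protocol article*

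**What the plan says.** The Current study section lists first, with binge eating frequency as primary outcome: "Noninferiority of the food-related antisaccade training without feedback compared with the original training including feedback". Superiority of each training over waitlist comes second.

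The Statistical methods section gives two elements for non-inferiority. The first is a test: "we perform one tailed-tests with an alpha-level of 0.025". The second is added to it as a comparison, namely whether the "confidence interval of the inhibitory control training without feedback includes the effect of the inhibitory control training with feedback which resembles the non-inferiority margin". The text does not say how the two combine or which outcome of the comparison counts in favour of non-inferiority. For each training against waitlist it says "we conduct two-sided tests with an alpha-level of 0.05".

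The primary model takes the "number of binge eating episodes during the last four weeks in a linear mixed model with baseline adjustment at T8 and T9". The Sample size section relies on the earlier trial, where "20 patients per group were sufficient to detect significant effects with a moderate effect size between two groups" ("treatment vs. active comparator; d ≈ 0.7"). Neither section gives a numerical margin, a scale for one, or an acceptable loss.

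**The concern.** A non-inferiority claim needs three things: a between-arm contrast with its own standard error, a loss fixed in advance as the largest that is acceptable, and a confidence interval that excludes that loss. The stated criterion has none of them. The interval belongs to one arm. The so-called margin is the other arm's effect, which is known only once the data are in and is not a loss. The comparison asks about inclusion, whereas a non-inferiority conclusion rests on exclusion.

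This bears on the trial's lead question. The Discussion says that outcomes comparable to the training with feedback could open the way to a digital intervention without eye tracking. A criterion that cannot tell a small loss from an imprecise estimate would not support that step.

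**Working it through.** **Inputs.** From the Sample size section: 20 per group from the earlier trial, 5% dropout, 63 patients (21 per arm), d ≈ 0.7. From Statistical methods: one-tailed 0.025 and the interval comparison. The article gives neither a margin nor an SD, so everything below is in SD units and the true losses are assumptions.

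**The plan's own figure.** 3 × 20 = 60, and 60 × 1.05 = 63, so the stated total reproduces. No margin enters it.

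**Reading A: inclusion supports non-inferiority.** Let m₁, s₁ be the mean and SD without feedback and m₂ the mean with feedback, with n per arm. The check is met when

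|m₁ − m₂| ≤ t(0.975, n−1) × s₁/√n.

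At n = 20 and SD 1 the allowed gap is about 2.093/√20 = 0.47 SD. A 95% CI for the difference has half-width 2.024 × √(2/20) = 0.64 SD. The gap is the narrower of the two because m₂ is treated as known.

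Simulated share of trials meeting the check (interval check alone, normal data, equal SDs, raw means):

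| True loss without feedback, n = 20 | Check met |
|---|---|
| 0 | about 85% |
| 0.35 SD | 63% |
| 0.5 SD | 45% |
| 0.7 SD | 23% |

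| n per arm, true loss 0.35 SD | Check met |
|---|---|
| 10 | 75% |
| 20 | 63% |
| 40 | 44% |
| 80 | 21% |

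A better-informed trial passes less often at the same true loss, which is the behaviour of a non-significance rule. The check is also two-sided: if no feedback is truly better by 0.7 SD, it is met in only 23% of trials at n = 20. Reading the check as the CI of the difference including zero raises the pass rates, to 66% at a loss of 0.5 SD and 42% at 0.7 SD.

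**Reading B: the comparator's effect is the boundary of the one-tailed test.** The margin on the difference scale is then zero, and the test is one of superiority. With equal arms it passes 2.5% of the time, while the Reading A check passes about 85%. The two criteria are practically exclusive. Superiority needs m₂ − m₁ > 2.024 × √((s₁² + s₂²)/20), and inclusion needs |m₁ − m₂| ≤ 2.093 × s₁/√20. Both can hold only if s₂²/s₁² < (2.093/2.024)² − 1 ≈ 0.07. With equal true SDs, no simulated trial at n = 20 met both.

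**Reading C: the margin is the whole effect of training against waitlist.** An allowable loss equal to the entire effect means that non-inferior says only better than no treatment. The separate waitlist comparison already addresses that question.

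**What a conventional criterion could deliver at n = 20.** With true difference zero and one-sided 0.025, power = Φ(margin/√(2/20) − 1.96):

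- margin 0.3 SD: Φ(0.949 − 1.96) = 16%
- margin 0.5 SD: Φ(1.581 − 1.96) = 35%
- margin 0.7 SD: Φ(2.214 − 1.96) = 60%

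Power of 80% needs a margin of (1.960 + 0.842) × √(2/20) ≈ 0.89 SD.

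**The case against.** The strongest reply is that the article never says inclusion means acceptance. A reader might infer that the rule is flatly inverted, but the sentence only announces a comparison. In conventional practice a CI that includes the margin means non-inferiority is not shown, and the wording could be meant that way. This stands: the inversion is the most natural reading, not a stated rule. It does not rescue the criterion, because with the comparator's effect as margin the conventional direction becomes Reading B or C.

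A reader might also set 63% or 45% against the nominal 2.5% and call the error rate inflated. The documents do not support that. The 2.5% belongs to the one-tailed test, the percentages describe the interval check alone, and a non-inferiority error rate exists only relative to a margin, which is absent. Nor is 0.35 SD a benchmark from the plan: it is half of a d from a trial in which both arms were trained, and is used here only as an assumed loss.

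It is tempting to add that the earlier trial cannot supply a margin because it had no untreated arm ("we also investigate the superiority of the treatment against a waitlist control which was absent in the previous trial"). The plan does not claim to take its margin from that trial, so this is no error in it.

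Finally, a numerical margin may stand in an analysis plan that is not shown. Its absence from a condensed article is therefore not the point. The article itself names what serves as the margin and what is compared with it, and an analysis plan with a proper margin would contradict that text.

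**Conclusion.** The criterion as published is invalid for the first-listed hypothesis on the primary outcome and must be corrected. It sets no allowable loss, leaves out the comparator's sampling error and does not state the direction of the decision. None of the three readings gives a non-inferiority test that preserves part of the training effect, and the inclusion check conflicts with a zero-margin one-tailed test.

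The size of the problem can only be illustrated. On the natural reading, a true loss of 0.5 SD would meet the check in about 45% of trials at 20 per arm, and smaller trials would meet it more often. This assumes normal data, equal SDs and no baseline adjustment, whereas the plan uses a baseline-adjusted mixed model, possibly a generalized one, for episode counts. Adjustment would change the percentages but not their direction.

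**What to change.** Delete the one-arm interval comparison. In its place:

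1. Define the contrast as without minus with feedback (a difference in episodes, or a rate ratio if the generalized model is used), estimated from the primary model at one named primary time point.
2. Prespecify one numerical margin on that scale, with its source and justification, before any unblinded look at the data.
3. Claim non-inferiority only if the two-sided 95% CI of the contrast lies wholly on the acceptable side of the margin. This is equivalent to the one-sided 0.025 test already planned.
4. If no margin can be justified, report the contrast with its 95% CI and make no non-inferiority claim.

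The change is one of wording and needs no new data. The cost lies in what the trial can conclude: with about 20 per arm, the CI half-width is about 0.64 SD before baseline adjustment, so non-inferiority will be hard to claim for any moderate margin. The protocol should say so.

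### The plan does not fix one coherent primary parameter: it pairs a baseline-adjusted model at T8 and T9 with time-by-treatment interactions and with changes from T0

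*Protocol article*

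**What the plan says.** The first paragraph of Statistical methods puts the four-week binge count "in a linear mixed model with baseline adjustment at T8 and T9". It then gives level and sidedness for the arm comparisons. For non-inferiority of training without feedback, "we perform one tailed-tests with an alpha-level of 0.025"; for each training arm against waitlist, "we conduct two-sided tests with an alpha-level of 0.05". It does not say which model quantity these tests use.

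The second paragraph opens with "In secondary analyses, a mixed model approach will be used to analyze the secondary outcomes also with baseline adjustment", continues with "Effect sizes will be analyzed and reported for primary and secondary outcomes", and closes with "Primary parameters will be time vs. treatment interactions at several time points after baseline".

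The section Primary outcome measure describes the comparison as change: "We compare changes in binge eating episodes at the four weeks follow-up (T8) to baseline (T0"), and likewise "at the 3-months follow up (T9) to baseline (T0"). Table 1 shows the EDE binge count at T0, T8 and T9 only. The article nowhere says whether T0 enters the model as a covariate or as an outcome level.

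**The concern.** The sentence on primary parameters is the only one that ties the conclusions to a term in the model. What that term means depends on how T0 enters, and the article leaves this open.

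On the usual reading of baseline adjustment, T0 is a covariate and only T8 and T9 are modelled as outcomes. There is then one interaction per pair of arms, and it does not address the aims under Current study (non-inferiority without feedback; superiority of each training arm over waitlist). On the reading suggested by changes from T0, the interaction does address the aims, but it is a different and less precise estimator than the adjusted model provides.

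As written, the text therefore permits a choice between different tests of the same hypotheses after the data are seen. The same holds for secondary outcomes measured at both T7 and T8, such as the BDI-II, TFEQ and WHO-5.

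**Working it through.** **Inputs from the article.** Outcome times are T0, T8 and T9 (Table 1). The Sample size section gives 20 evaluable patients per arm and d of about 0.7. That section's own figure is consistent (20 × 1.05 = 21 per arm, 63 in total), but it does not bear on this point. The article gives no power figure for any parameter.

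**Assumptions, not in the article.** Two arms compared, normal outcome, unit SD, complete data, a common correlation r among T0, T8 and T9 of 0.3, 0.5 or 0.7, two-sided alpha 0.05, and 4,000 simulated trials per setting.

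Write D0, D8 and D9 for the difference in arm means at each visit (training minus comparator; negative means benefit).

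**Reading A: T0 as covariate, outcomes at T8 and T9.** The interaction is D9 − D8.
- Equal benefit: −0.7 − (−0.7) = 0.
- Benefit halved by T9: −0.35 − (−0.7) = 0.35, which measures fading and not efficacy.
- Non-inferiority: if training without feedback is worse by k at both visits, the interaction is k − k = 0, so the inferiority does not show.

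**Reading B: T0 as an ordinary outcome level.** The interactions are D8 − D0 and D9 − D0. Each estimates the treatment effect (simulated mean about −0.70 at T8). The variance is (2σ²/n) × 2(1 − r).

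**Reading C: baseline-adjusted contrast at a visit.** For T8 this is D8 − r·D0, with large-sample variance (2σ²/n) × (1 − r²). A longitudinal model with T0 as an outcome and a common baseline mean across arms gives the same contrast and variance when the covariance is known and data are complete.

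**Variance of B relative to C:** 2(1 − r)/(1 − r²) = 2/(1 + r).
- r = 0.3: 1.4/0.91 = 1.54
- r = 0.5: 1.0/0.75 = 1.33
- r = 0.7: 0.6/0.51 = 1.18

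**Simulated rejection rates with d = 0.7 at both T8 and T9, 20 per arm:**

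| r | A: T8-to-T9 interaction | B: T0-referenced interaction at T8 | C: baseline-adjusted contrast at T8 |
|---|---|---|---|
| 0.3 | 5% | 45% | 61% |
| 0.5 | 5% | 58% | 69% |
| 0.7 | 6% | 80% | 84% |

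Column A is the alpha level, because the tested quantity is truly zero. When the effect halves from 0.7 to 0.35, the interaction in A rejects in 15%, 19% and 30% of trials for the three correlations.

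**The case against.** Much can be said for the plan. That T0 is a covariate is inferred from the phrase on baseline adjustment; the word does not appear. The plural, interactions at several time points after baseline, fits T0-referenced interactions or visit-specific arm contrasts better than the single T8-to-T9 coefficient. The primary outcome section also points to T0. A constrained longitudinal model would make baseline adjustment and post-baseline interactions one coherent analysis without loss of precision. Nor need the word changes conflict with adjustment: in a linear model that adjusts for T0, analysing the change or the follow-up value gives the same arm contrast. The arm comparisons are listed separately, the sentence stands at the end of a paragraph that begins with secondary analyses, and this is a condensed article.

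These points rule out stronger conclusions that a reader might draw:
- **That the trial would declare a sustained benefit null.** This follows only under Reading A, and only if the separately stated arm comparisons are tested on the interaction.
- **That a fading benefit would be declared significant.** Rejection is 15 to 30% in the case examined.
- **That T0 cannot be both an outcome level and the means of adjustment.** The constrained model does exactly that.

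They do not remove the ambiguity. The constrained model is nowhere stated. The separate comparisons give alpha and sidedness but no model quantity. The sentence speaks of primary parameters, and the one shortly before it covers primary and secondary outcomes. If it applies only to secondary outcomes, the same difficulty arises between T7 and T8. Nor is this a detail merely left to a fuller document: the article names a parameter, and that parameter does not fit the usual reading of its own model.

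**Conclusion.** The point holds as an ambiguity in the primary parameter that should be settled before analysis. It does not show that the planned primary test fails to measure efficacy.

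Under one reading the named parameter is the wrong test for the aims. Under the ordinary alternative it is a valid test that is less precise than the adjusted contrast, and the loss shrinks as the baseline correlation rises: at T8 it is 16, 11 and 4 percentage points of power (61 − 45, 69 − 58, 84 − 80). Only an unstated constrained model avoids both problems.

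The algebra of Reading A and the ratio 2/(1 + r) need only equal variances at T0 and follow-up and a linear model. The power figures also rest on the assumed correlations, normality, complete data, and d = 0.7 carried over from the pilot comparison to the arm comparison here.

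**What to change.** Replace the sentence on primary parameters with wording such as:

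> The primary parameters are the baseline-adjusted differences between arms at T8 and at T9 (without minus with feedback; each training arm minus waitlist), estimated as visit-specific contrasts from the model with arm, visit, arm-by-visit and T0 adjustment (T0 as covariate or, equivalently, a baseline mean constrained equal across arms). The change of the arm difference between visits is descriptive.

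State which of the two forms of T0 adjustment will be used. Align the description of changes under Primary outcome measure with this, and use the same wording for secondary outcomes that have more than one post-baseline visit.

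The cost is one or two sentences. Data collection and sample size are unaffected, and the emmeans package already listed in Statistical methods produces these contrasts.
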